## Methods/design

### Setting and design

This study is a multicentre, randomized, double-blinded, placebo-controlled, parallel-group, 6-week treatment, clinical trial. Eligible participants will be randomly assigned to an intervention group (Antianxiety Granule) or placebo group at a ratio of 2:1. The participants will be recruited from the following six hospitals: Shanghai Municipal Hospital of Traditional Chinese Medicine, Shanghai Seventh People’s Hospital, Shanghai Chinese and Western Medicine Hospital, The Fifth People’s Hospital of Shanghai, Fudan University, Jingan District Hospital of Traditional Chinese Medicine, and Yangpu District Hospital of Traditional Chinese Medicine. The study consists of three periods: a 1–7-day screening period, a 6-week primary treatment period, and a 1-week follow-up period. Participants will be assessed at baseline and at the 2nd, 4^th^, and 6th week after the initiation of the intervention. Follow-up assessments will be conducted 1 week after the last visit by face-to-face interviews or by telephone (Fig. 1). In this study, the clinical efficacy of Antianxiety Granule will be assessed for the treatment of GAD by examining changes in the Hamilton anxiety scale (HAMA) score, state-trait anxiety inventory (STAI) score and the TCM symptom scale in patients with GAD who receive daily TCM treatment. The flowchart of the study process is presented in Fig. 1, and the timing of the treatment visits and data collection is presented in Table 1.

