### Sample size

A sample size of 252 participants will be recruited on the basis of the pre-post trial. On the basis of previous results and considering an anticipated participant dropout rate of 20%, with a significance level of 0.05, 252 patients will be needed. These 252 patients will be randomly divided into two groups (168 participants in the Antianxiety Granule group and 84 participants in the placebo group, in a ratio of 2:1).

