### Outcomes

#### Primary outcome

The primary outcome measure will be a change in the HAMA score [19]. The HAMA scale is the most widely used assessment tool for anxiety disorders in psychiatric clinical and scientific research. The HAMA scale is a 14-item observer-rating questionnaire that can be categorized into two orthogonal groups, “psychic” and “somatic” anxiety. The outcome will be assessed by the difference in the HAMA score from the baseline.

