### Statistical analyses

The main analysis will follow the intention-to-treat (ITT) principle and will be done as follows: the full analysis set (FAS) will include the randomized participants who received any treatment and completed at least one follow up. The per-protocol set (PPS) will include patients who complied with the protocol. Only when the minimum compliance rate of participants who received the investigational drug is 80% will we use the PPS. Participants who have at least one randomized treatment will be included in the ITT and safety set (SS). To estimate missing primary outcome variables, data from the last study will be used as the final result following the last observation carried forward (LOCF) principle. Data will be analysed using the statistical software SAS version 9.4 or SPSS 20.0.

Sociodemographic variables will be analysed by the *t* test for continuous variables. Matched data will be compared using the Wilcoxon test, and categorical variables will be analysed using the chi-squared test. Change across time of the primary and secondary outcomes will be analysed by repeated measures analysis of variance (ANOVA). We will use ANOVA for randomized block design if the variance and covariance matrix meet the sphericity assumption. ANOVA for repeated measurement data may have two types of error: errors among subjects are the errors corresponding to treatment, and errors within subjects are the errors corresponding to time and the interaction between treatment and time. Significance is will be accepted when the two-sided alpha level is 0.05.

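### With 2:1 allocation, the planned ANOVA's error terms pooled over arms give a biased standard error if the granule changes the spread of on-treatment HAMA scores, and the sphericity condition does not cover this

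*Protocol article*

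**What the plan says.** The primary outcome is change in HAMA: "The outcome will be assessed by the difference in the HAMA score from the baseline". Under Setting and design, "Participants will be assessed at baseline and at the 2nd", 4th and 6th weeks, so there are four on-site measurements per patient. Under Sample size the arms are fixed at "168 participants in the Antianxiety Granule group and 84 participants in the placebo group, in a ratio of 2:1".

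Statistical analyses names repeated measures ANOVA for the primary and secondary outcomes and describes two error terms. For the first it says "ANOVA for repeated measurement data may have two types of error: errors among subjects are the errors corresponding to treatment". The second, within subjects, serves time and the treatment-by-time interaction. One condition is attached: "We will use ANOVA for randomized block design if the variance and covariance matrix meet the sphericity assumption". The test level is two-sided 0.05. The article names no arm-specific variance, robust standard error or check of equal spread between arms. It gives no HAMA SDs and does not mention confidence intervals.

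**The concern.** A single between-subject error and a single within-subject error both assume that the two arms share one covariance matrix. With arms of equal size, failure of that assumption does little harm to the arm comparison. At 2:1 the protection goes. The pooled variance is weighted towards the larger granule arm, while the variance of the difference in means depends more on the smaller control arm.

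Randomisation makes spread alike at baseline but does not keep it alike on treatment. If some patients respond and others do not, or if scores move towards the floor of the scale, the granule arm may become more or less variable than control. If control is the more variable, the standard error is too small and the test rejects too often. If the granule arm is the more variable, the standard error is too large and power is lost. Sphericity is a condition on the pattern of within-person differences over time. It is not a condition on equality between arms.

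**Working it through.** **The plan's own figure.** 168 + 84 = 252 and 168/84 = 2, so the split is consistent. With the stated 20% dropout, 252 × 0.8 = 201.6 patients remain, about 134 v 67. The total itself cannot be rebuilt, because the section gives no effect size, SD or power. It also gives no SD by arm, so a range is assumed below.

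**Formula.** For a comparison of two means with outcome variances v_g (granule) and v_c (control):
- pooled variance s² = (167·v_g + 83·v_c)/250
- q² = s²(1/168 + 1/84) / (v_g/168 + v_c/84)
- rejection rate when the means are equal = 2[1 − Φ(1.96·q)]

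With two arms of 126, q = 1 whatever the variances. The size of the problem therefore comes from the 2:1 ratio.

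**Simplest case, SD ratio applied directly to the outcome.** Control SD 1.25 or 1.5 times granule SD gives 6.9% or 8.5%. Granule SD 1.25 or 1.5 times control SD gives 3.5% or 2.6%. At 134 v 67 the results agree to within 0.0002. SD ratios of 0.9 to 1.1 give 4.3% to 5.9%. Used for the repeated measures test, these figures are too large, because they would let spread differ at baseline as well.

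**Treatment test with equal baseline spread.** Assume four visits, correlation 0.5, SD 1 at baseline in both arms, and SD r at weeks 2, 4 and 6 in the more variable arm. The treatment effect is tested on each patient's mean over visits. Its variance is (1 + 3r + 6r²)/16:
- r = 1: 10/16 = 0.625
- r = 1.25: 14.125/16 = 0.8828
- r = 1.5: 19/16 = 1.1875

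For control 1.25: s² = (167 × 0.625 + 83 × 0.8828)/250 = 0.7106. The pooled variance of the difference is 0.7106 × 0.017857 = 0.01269. The true variance is 0.625/168 + 0.8828/84 = 0.01423. So q = √(0.01269/0.01423) = 0.944, and the rejection rate is 2[1 − Φ(1.851)] = 6.4%. The other cases follow in the same way.

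**Treatment-by-time.** This was simulated under the same assumptions with no mean differences. Ranges are over separate simulation runs of 5,000 to 40,000 trials.

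| More variable arm, r | q (treatment) | Treatment, formula | Treatment, simulated | Treatment-by-time, simulated |
|---|---|---|---|---|
| Control, 1.25 | 0.944 | 6.4% | 6.2–6.7% | 7.0–7.5% |
| Control, 1.5 | 0.901 | 7.7% | 7.3–8.0% | 9.7–10.2% |
| Granule, 1.25 | 1.059 | 3.8% | 3.5–4.1% | 3.0–3.4% |
| Granule, 1.5 | 1.110 | 3.0% | 2.9–3.4% | 1.9–2.2% |

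If the control SD ratio instead grows linearly from 1 at baseline to its full value at week 6, the rates are 6.2% and 6.3% (1.25) and 7.1% and 8.3% (1.5). Growing to 1.1, they are 5.2% and 5.7%.

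**Controls.** At 126 v 126 with the same unequal SDs, both tests stay at 4.9–5.6%. At 168 v 84, an unequal-variance test of the week-6 change stays at 4.7–5.6%.

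**Sphericity.** Where the arms differ by a constant factor at all visits, Mauchly's test rejected in only 5–9% of simulated trials, although the variances differed by up to about 2.2-fold (1.5² = 2.25). Where spread differs only after baseline, it rejects more often: about 10% and 27% (control 1.25 and 1.5), and 24% and 59% (granule 1.25 and 1.5). It then reacts to variance that changes over time. It also rejects often at 126 v 126 (16–17% and 44%), where the arm comparison is sound. Either result says nothing reliable about equality between arms.

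**The case against.** The strongest reply is that common covariance is the ordinary assumption of this ANOVA, that the same could be said of most 2:1 trials analysed by t test or ANCOVA, and that variance options belong in an analysis plan that is not shown. This stands in part. If that plan already names arm-specific or robust variance, the point is met. But the article does not leave the matter open: it names the method, describes one error term for each type of effect and attaches one condition. That stated choice fits the 2:1 design badly.

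The reply also says that the article gives no evidence that spread will differ, or in which direction. This is right, and the size is conditional for that reason. An unknown direction is also a reason to settle the variance before unblinding.

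Four stronger readings are tempting, and the document does not support them:
- *Any difference in spread spoils the p-value.* It does not. Ratios of 0.9 to 1.1 move the level by less than one percentage point.
- *An inert granule would be declared effective more than 5% of the time.* If it affects no patient, the arms have the same distribution and the level stays near 5%. The inflated rates need a granule that alters spread while mean scores stay equal.
- *The planned confidence intervals are wrong.* The article mentions none. The concern reaches intervals only if they are reported from the pooled error.
- *The sphericity check is blind to unequal arms.* It can react when spread changes over time, but it does not identify a difference between arms and would not correct the treatment test.

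**Conclusion.** The point holds as a conditional, moderate weakness in the primary analysis. Pooled error terms and 168 v 84 allocation leave the HAMA comparison exposed if treatment changes spread, and the one stated condition does not address this. At an on-treatment SD ratio of 1.25 the nominal 5% becomes roughly 6–7.5% or 3–4%, depending on which arm is the more variable. At 1.5 it becomes roughly 7–10% or 2–3.5%.

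These figures assume normal scores, correlation 0.5, equal baseline SDs, and four visits including baseline in the model. None of these is given in the article as a HAMA figure. The direction cannot be predicted from the document. Within about 10% in SD, the matter can be ignored.

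**What to change.** Keep the repeated measures comparison, but state that the primary HAMA p-value, and any interval reported, will rest on variances that may differ by arm. Two routes do this:
- a mixed model with covariance estimated separately by arm, for example in SAS 9.4 with REPEATED / GROUP=arm and Satterthwaite or Kenward-Roger degrees of freedom;
- heteroscedasticity-robust standard errors, either sandwich errors for the model or an unequal-variance test for the change at a single visit.

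The pooled-error ANOVA can stay as a supporting analysis. The sphericity condition is not needed for a mixed model with an unstructured matrix.

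The cost is a few degrees of freedom and a small change to the analysis code and text. If the arms prove equally variable, the result hardly changes. Statistical analyses also allows SPSS 20.0, so the text should say which package runs the primary model, since the first route is set out here for SAS. The choice should be written down before unblinding.

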### Clinical trial registration

The trial was registered under the registration number ChiCTR1800016039 (http://www.chictr.org.cn/showproj.aspx?proj=27210) on 8 May 2018. The study was approved by the Ethics Committee of the Shanghai Municipal Hospital of Traditional Chinese Medicine (2017SHL-KY-14).

## Discussion

In the first nationwide survey of mental disorders in China, it was found that anxiety disorders were the most prevalent class of lifetime disorders (7.6%) [22]. GAD is a kind of anxiety disorder that typically begins in adulthood. Onset before puberty is rare, with only 5% of cases developing by the age of 13 years. Onset of GAD before adulthood is uncommon, occurring in fewer than 25% of cases. The clinical course is more persistent in low-income countries. Lifetime comorbidity is high (81.9%), and prevalence estimates vary widely across countries; lifetime prevalence rates in high-income countries are higher than those in middle-income and low-income countries [4]. With rapid economic development in China, Chinese people are more likely to suffer from pressure, anxiety, mood disorders, and related problems. Finding an effective therapeutic method for preventing and combating anxiety disorders is extremely important.

In recent years, several studies have indicated that TCM has a good effect on mental disorders. Antianxiety Granule has been widely prescribed for anxiety symptoms in specialist clinics. The purpose of Antianxiety Granule is to soothe the liver, regulate *qi*, enliven the spleen with aroma, activate the blood and tranquilize the body. In our preliminary studies, Antianxiety Granule, which is composed of *Cyperi rhizoma, Amomum aurantiacum, Cinnamomi cortex, Curcumae radix, Radix salviae, Gardeniae fructus, licorice, Polygala tenuifolia, Albizia bark, Polygoni multiflori caulis and daylily*, has been shown to effectively ameliorate symptoms of anxiety and insomnia in patients with GAD.

In our study, professional researchers are trained to specialize in assessment, which can improve the reliability and generalizability of the results. The trial will be conducted in a clinical outpatient setting with experienced clinicians, and participants will be recruited from the patient base of the other five hospitals involved in the trial. The purpose of this multicentre, randomized, double-blind, placebo-controlled, parallel-group trial is to evaluate the efficacy and safety of Antianxiety Granule compared to a placebo in patients with GAD in Shanghai. The results from the study will provide meaningful information and evidence for clinical practice and to design a confirmative, reasonable RCT in the near future. This study will confirm the safety and efficacy of the TCM Antianxiety Granule and evaluate if Antianxiety Granule can improve distressing symptoms of anxiety.

### Limitations

The RCT still has several design limitations. First, the sample size is relatively small, and the 1-week follow-up phase is short. We will be unable to estimate the recurrence of anxiety after long-term withdrawal. Second, the pathophysiology of GAD has not been clarified; only clinician rating scales, which lack an objective index to judge the effect of TCM treatment on GAD, have been used to measure effects. Finally, the 6-week treatment cycle in this study is relatively short. Bearing these limitations in mind, we will make a more rational treatment cycle and follow-up period to investigate the efficacy of Chinese herbs in patients with anxiety disorder.

## Trial status

This RCT was registered under the number ChiCTR1800016039 (http://www.chictr.org.cn/showproj.aspx?proj=27210) on 8 May 2018. The central ethical approval was obtained from the Ethics Committee of the Shanghai Municipal Hospital of Traditional Chinese Medicine (approval no. 2017SHL-KY-14) on 13 December 2017, and we will not begin recruiting at other centres in the trial until local ethical approval has been obtained. This protocol, version 2, was approved on 2 May 2018. The first participant was randomized in August 2018, and recruitment is ongoing. The final results will be reported in the following year.

## SPIRIT guidelines

Please see Table 1 for a copy of the Standard Protocol Items: Recommendations for Interventional Trials (SPIRIT) figure. The SPIRIT checklist can be found as Additional file 1.

## Data Availability

The datasets used or analysed in the current study are available from the corresponding author upon reasonable request.

## Abbreviations

AEs: Adverse events
ALT: Alanine aminotransferase
ANOVA: Analysis of variance
AST: Aspartate aminotransferase
BUN: Blood urea nitrogen
CRF: Case report form
GAD: Generalized anxiety disorder
HAMA: Hamilton anxiety scale
HAMD: Hamilton depression scale
ITT: Intention to treat
STAI: State-trait anxiety inventory
TCM: Traditional Chinese medicine
